**Appendix 3**

**Table 2 Pelvic Pain Score Sheet**

Number： Name：

ID： Tel：

Pain characteristics

1. Please describe your pain situation, such as frequency, duration, and intensity of the pain.

1. What do you think is the cause of the pain?

3、Has there been any event related to the onset of pain? A.Yes B.No

If so, what is the related event?

1. How long has this been going on?
2. The following symptoms are graded based on the severity of the past week. Please √ the appropriate box.

| Symptoms | [figure not shown] | | | | | | | | | | |
| --- | --- | --- | --- | --- | --- | --- | --- | --- | --- | --- | --- |
|  | 0 | 1 | 2 | 3 | 4 | 5 | 6 | 7 | 8 | 9 | 10 |
| How do you evaluate pain? |  |  |  |  |  |  |  |  |  |  |  |
| Ovulation pain (mid-menstrual cycle) |  |  |  |  |  |  |  |  |  |  |  |
| Premenstrual abdominal pain |  |  |  |  |  |  |  |  |  |  |  |
| Premenstrual pain (no spasms) |  |  |  |  |  |  |  |  |  |  |  |
| Deep dyspareunia |  |  |  |  |  |  |  |  |  |  |  |
| Groin pain when lifting leg |  |  |  |  |  |  |  |  |  |  |  |
| Post-coital pain lasting hours or days |  |  |  |  |  |  |  |  |  |  |  |
| Pain when holding urine |  |  |  |  |  |  |  |  |  |  |  |
| Muscle/joint pain |  |  |  |  |  |  |  |  |  |  |  |
| Menstrual cramping pain |  |  |  |  |  |  |  |  |  |  |  |
| Pain disappears after menses |  |  |  |  |  |  |  |  |  |  |  |
| Burning pain in the vagina after sex |  |  |  |  |  |  |  |  |  |  |  |
| painful urination |  |  |  |  |  |  |  |  |  |  |  |
| backache |  |  |  |  |  |  |  |  |  |  |  |
| migraines |  |  |  |  |  |  |  |  |  |  |  |
| seating pain |  |  |  |  |  |  |  |  |  |  |  |
| Overall score |  | | | | | | | | | | |

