Appendix 6 [3](#_Toc15674)8

[Appendix 7 4](#_Toc8090)1

Plan Summary

| Research Title | Peripheral combined central dual-target magnetic stimulation for rehabilitation of chronic pelvic pain syndrome with psychosomatic disorders: Study protocol for a randomized controlled trial |
| --- | --- |
| Principal Investigator | Deputy Chief Physician [name] |
| Research Purpose | This study aims to evaluate the effectiveness and safety of repeated peripheral magnetic stimulation (rPMS) combined with repeated transcranial magnetic stimulation (rTMS) in treating patients with pelvic pain syndrome accompanied by psychological disorders. It will assess the impact of dual-target magnetic stimulation on patients' pelvic pain scale/NIH-CPSI scores, depression, anxiety, and stress (DASS-21) scores, as well as the SF-36 quality of life scale, and the effects on pelvic floor muscle surface electromyography and pudendal nerve motor evoked potentials. Additionally, it will compare the effects of dual-target magnetic stimulation and peripheral magnetic stimulation on pain levels, psychological status, and quality of life in patients with chronic pelvic pain syndrome accompanied by psychological disorders, providing a basis for clinical treatment options. |
| Main evaluation indicators (efficacy indicators) | Pelvic Pain Scale (Female) / NIH-CPSI (Male) |
| Secondary evaluation indicators (efficacy indicators) | Surface electromyography of the pelvic floor muscles  Pudendal nerve motor evoked potentials  Depression Anxiety and Stress Scale (DASS-21)  SF-36 Quality of Life Scale |
| Safety indicators | Complete Blood Count (CBC)  Liver and kidney function  Electrocardiogram |
| Selection Criteria | (1) Meets the diagnostic criteria for Chronic Pelvic Pain Syndrome (CPPS) according to the European Association of Urology (EAU) guidelines for chronic pelvic pain (2022 edition).  (2) Age: 18-70 years old.  (3) Generalized Anxiety Disorder or Major Depressive Disorder that meets DSM-5 criteria.  (4) No significant pathological changes were observed in the physical examination and auxiliary examinations.  (5) No other treatments except for oral medications in the three months prior to the visit.  (6) The patient is informed and voluntarily participates in the study. |

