3.1 Inclusion Criteria

(1) Meets the diagnostic criteria for Chronic Pelvic Pain Syndrome (CPPS) according to the European Association of Urology (EAU) guidelines (2022 edition).

(2) Age: 18-70 years old;

(3) Can be clearly diagnosed as Generalized Anxiety Disorder or Major Depressive Disorder according to DSM-5 criteria;

(4) No significant pathological changes were observed in the physical examination and auxiliary examinations;

(5) No other treatments except for oral medications within 3 months prior to the visit;

(6) The patient is informed and voluntarily participates in the study.

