6.5 Treatment Plan

A treatment course will consist of 20 sessions, with five sessions per week, one session each day. The completion of the 20th treatment will mark the end of the course. Follow-up will be scheduled 8 weeks after the end of the course. During the study, patients may receive oral medication, and the specific medication and dosage must be recorded at the time of enrollment. If there are any significant adjustments to the type and dosage of the medication, they need to actively inform the therapist.

7. Follow-up Plan

(1) Assessment, follow-up plan and content: Patients need to return to the hospital for evaluation before treatment, at the end of each weekly treatment, and 8 weeks after the treatment course ends. The assessment includes the patient's pelvic pain score/NIH-CPSI, DASS-21 scale, SF-36 scoring scale, pelvic floor surface electromyography, and pudendal nerve motor evoked potentials.

(2) Establish a complete database and implement a follow-up mechanism managed by dedicated personnel.

(3) Follow-up time points: Before treatment, at the end of each weekly treatment, and up to 8 weeks after the end of the treatment course.

(4) Outside of the time points for in-hospital assessments and follow-up visits, dedicated follow-up medical staff will conduct tracking follow-ups through phone calls, written questionnaires, emails, and other forms.

8. Evaluation Indicators for Research Results

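### Half of the rows on the women's primary pain sheet can be rated only if the past week held a given menstrual phase or intercourse, and the form cannot separate no pain from no occasion

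*Protocol*

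**What the plan says.** The Plan Summary and section 8.1 make the Pelvic Pain Scale the primary efficacy measure for women; men have the NIH-CPSI. The women's sheet is in Appendix 3, Table 2. Its severity grid carries the instruction "The following symptoms are graded based on the severity of the past week. Please √ the appropriate box" and lists 16 rows, each on a 0-10 scale, followed by a single cell for the overall score.

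Some rows can be rated in any week. Others cannot, for example "Premenstrual abdominal pain" and "Post-coital pain lasting hours or days". The grid has no column for a symptom that did not arise or does not apply, and no scoring formula is given.

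Section 7 sets the timing: "Follow-up time points: Before treatment, at the end of each weekly treatment, and up to 8 weeks after the end of the treatment course". The schedule in Appendix 2 agrees, with the sheet due at t0, t1-t4 and t5. Section 3.1 admits patients by "Age: 18-70 years old", so postmenopausal women are eligible.

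**The concern.** Eight rows depend on an occasion that a given week may not contain. When the occasion is absent, the woman can tick 0 or leave the row blank. A ticked 0 looks the same as a true absence of pain. A blank leaves the total undefined. The sum can then move between weekly visits although her pain is unchanged. Women who no longer menstruate can never rate five of the rows.

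The stake is precision. Each arm has 22 patients of both sexes (section 5.1), so the women are a smaller subset still, with little room for avoidable variance in the primary score. An analysis plan written later could set a rule for blanks, but it could not recover what a ticked 0 meant, because the form does not record it.

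**Working it through.** **1. Row count (Appendix 3, Table 2).**
- Cycle-bound, 5 rows: ovulation pain; two premenstrual rows; menstrual cramping; pain disappearing after menses.
- Intercourse-bound, 3 rows: deep dyspareunia; post-coital pain; vaginal burning after sex.
- Ratable in any week, 8 rows: overall pain; groin pain on lifting the leg; pain when holding urine; muscle/joint pain; painful urination; backache; migraines; pain when sitting.

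Total 5 + 3 + 8 = 16. Assuming a plain sum, the range is 16 × 10 = 160, of which 8 × 10 = 80 points depend on an occasion.

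**2. Attainable maximum on the sum.** All rows: 160. Postmenopausal: 160 − 50 = 110. Also sexually inactive: 110 − 30 = 80. Halving severity from 5 to 2.5 on every ratable row gives −2.5 × 16 = −40, −2.5 × 11 = −27.5 and −2.5 × 8 = −20. The same relative improvement has three different sizes.

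**3. Same pain, different weeks.** Hold every applicable row at 5 and score rows without an occasion as 0.

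| Week | Sum | Mean of applicable rows |
|---|---|---|
| No cycle event, no intercourse | 8 × 5 = 40 | 40/8 = 5 |
| Premenstrual only | 10 × 5 = 50 | 50/10 = 5 |
| Premenstrual and intercourse | 13 × 5 = 65 | 65/13 = 5 |

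**4. Size of the cycle part over the visits.** Assumptions, none of them from the protocol: all five cycle rows active at severity 5; 28-day cycle, SD 2.5 days between and 2 days within women; random phase at t0; 7-day windows ending on days 0, 7, 14, 21, 28 and 84; phases lasting 2 days (ovulation), 5 days (premenstrual, two rows), 4 days (menses) and 3 days (after menses). A row scores 5 if its phase overlaps the window and 0 otherwise.

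Analytic check for a regular 28-day cycle: a phase of d days overlaps a 7-day window with probability (d + 6)/28. The expected cycle contribution is 5 × (8 + 11 + 11 + 10 + 9)/28 = 5 × 49/28 = 8.75 points at every visit, so the expected change is zero. An individual woman's contribution runs from 0 to 20.

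Simulated change from t0 with no treatment effect:

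| | t1 | t2 | t3 | t4 | t5 |
|---|---|---|---|---|---|
| SD, all five rows at severity 5 | about 8 | 9.5 | about 8 | 5 | 7 |
| Share with a swing of 10 points or more | 33% | 54% | 32% | 13% | 27% |
| SD, only one premenstrual row and cramping active | 5.8 | 7.5 | 5.7 | 3.2 | 5.2 |

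The mean change stays within about 0.5 point of zero at every visit. The SD scales with severity: about 3 to 6 points at severity 3 and about 7 to 13 at severity 7. It is smallest at t4 because day 28 is one cycle after t0. With a perfectly regular 28-day cycle it all but vanishes at t4 and at t5 (84 = 3 × 28).

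**5. Intercourse rows.** A woman who scores 0 on these rows at t0 for want of an occasion, and later rates each of the three at 3 (assumed), gains 3 × 3 = 9 points on the sum.

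**The case against.** A reader might infer that cycle phase and menopausal status confound the treatment comparison, or that the t1-t3 course cannot be interpreted. The documents do not support either. Allocation is randomised within gender (section 5.2), phase at entry is unrelated to arm, and the expected change from phase alone is zero. Menopausal status is practically fixed over 12 weeks and adds no phase noise to a woman's own change. Comparisons between arms become noisier, not biased.

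A reader might also infer that improvement is counted as worsening when intercourse resumes. That would be bias, but it needs treatment to change sexual activity. The documents give no figure for how often, or in which direction, this happens, and the 9 points ignore any fall in the other rows. It remains a possibility only.

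The size is also open to challenge. The headline SDs need all five cycle rows active at equal severity and 0 ticked in every off-phase week. The protocol gives no SD for the women's total, so the share of variance lost is unknown. The total is assumed to be a plain sum. The after-menses row is worded as relief, so its scoring direction is unclear, yet the calculation treats it as ordinary severity.

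Finally, section 8.1 shows that menstrual and sexual pain are deliberately part of this scale, and scoring rules are often left to an analysis plan. Both points stand: they argue against dropping the eight rows from the primary score, and against faulting the missing formula by itself. They do not answer the form defect. Appendix 2 schedules an analysis of missing items, but a ticked 0 is not missing. Appendix 6 shows that the protocol can attach an item-level rule to a form, since it does so for the SF-36.

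**Conclusion.** The point holds as one of measurement precision. Completed as printed, the women's primary sheet lets 0 stand for both no pain and no occasion on 8 of 16 rows, which is 80 of 160 points if the total is a plain sum. Under the stated illustrative assumptions, phase alone gives an SD of change of about 8, 9.5, 8, 5 and 7 points at t1-t5. It is less when fewer rows are active and least at t4.

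The cycle part is avoidable noise between randomised arms. Bias would arise only if treatment altered sexual activity, which the documents leave unquantified. The finding does not make the weekly data unusable and does not affect the sample-size figure. It should be corrected, but it is not fatal to the trial.

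**What to change.** Add a box for did not occur this week / not applicable to the five cycle rows and three intercourse rows. Treat it as not applicable, never as 0. Score the women's total as the mean of applicable rows, and state the scoring direction of the after-menses row. Add a pre-specified sensitivity analysis on the eight rows that any woman can rate in any week, and report the cycle and intercourse rows separately.

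In the example of step 3 the mean is 5 in every week, and halving severity gives −2.5 for all three women in step 2. The mean does not remove the problem when rows differ in severity. With the eight constant rows at 3 and two premenstrual rows at 5, the sum moves from 24 to 34 and the mean from 3.0 to 34/10 = 3.4.

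The cost is one extra column and a scoring sentence, with no new visits. The downside is small: the set of rows in the mean can differ between visits, and the form departs slightly from its present layout. The fixed eight-row analysis covers this.

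Two larger changes are not recommended. Making the eight-row score the sole primary would change the intended construct, since three of its rows (migraines, muscle/joint pain, backache) are not specifically pelvic. A full-cycle recall for the cycle rows would need a second recall instruction and new data.

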**Appendix 4 Table 3 NIH-CPSI**

Number： Name：

ID： Tel：

The following symptoms are graded based on the severity of the past week. Please √ the appropriate box.

| **Pain or discomfort symptoms** | | None | Rarely | Occasionally | Frequently | Very common | Almost always |
| --- | --- | --- | --- | --- | --- | --- | --- |
| 1. Have you experienced pain or discomfort in the following areas? | | 0 | 1 | 2 | 3 | 4 | 5 |
| Perineal pain | |  |  |  |  |  |  |
| Didymalgia | |  |  |  |  |  |  |
| Glans penis | |  |  |  |  |  |  |
| Lumbosacral and suprapubic region | |  |  |  |  |  |  |
| 1. Pain or burning sensation during urination | |  |  |  |  |  |  |
| 1. Painful discomfort at or after ejaculation | |  |  |  |  |  |  |
| 1. Use numbers to describe the degree of pain or discomfort mentioned above.   No pain 0 1 2 3 4 5 6 7 8 9 10 worst possible pain | | | | | | | |
| **Urinary symptoms** | | None | Less than 1/5 | Less than half | About half | More than half | Almost every time |
|  |  | 0 | 1 | 2 | 3 | 4 | 5 |
| 1. Whether there is often a feeling of incomplete urination at the end of urination ? | |  |  |  |  |  |  |
| 1. Do you often feel the need to urinate again within 2 hours after urinating? | |  |  |  |  |  |  |
| **Symptom severity** | | None | Little | Some | A lot |  |  |
|  |  | 0 | 1 | 2 | 3 |  |  |
| 1. Do the above symptoms affect your daily life? | |  |  |  |  |  |  |
| 1. Are you always reminded of your symptoms? | |  |  |  |  |  |  |
| Quality of life | Very satisfactory | Satisfactory | Good | Just so so | Mostly unsatisfactory | Unhappy | Fearful |
|  | 0 | 1 | 2 | 3 | 4 | 5 | 6 |
| If left untreated, how do you think your life will be in the future? |  |  |  |  |  |  |  |
| Analysis of NIH-CPSI score results | | | | | | | |
| Pain and discomfort score:1+2+3+4=( ) | | Symptom impact scores on quality of life：7+8+9=( ) | | | | | |
| Voiding Symptom Score：5+6=( ) | |  | | | | | |
| Symptom severity：1+2+3+4+5+6=( ) | | Mild:0~9 | | Moderate:10~18 | | Severe:19~31 | |
| Overall rating:  1+2+3+4+5+6+7+8+9=( ) | | Mild:1~14 | | Moderate:15~29 | | Severe:30~43 | |

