8.1 Main Efficacy Indicator: Pain Score

(1) Pelvic Pain Rating Scale (for women): It includes the patient's basic information, detailed changes in symptoms, and the effectiveness of previous treatments. It uses pain exacerbated and relieved by sexual activity and menstruation as the starting point for medical history inquiries. Additional details include symptoms related to exercise, urinary, and bowel function.

(2) NIH-CPSI (for men): It mainly consists of three parts, assessing pain or discomfort caused by chronic prostatitis, urinary symptoms, and the impact on quality of life, with a total of nine questions. It is characterized by objectivity and convenience, is quickly accepted by patients, and can provide important references for research and clinical work.

8.2 Secondary Efficacy Indicators:

(1) Anxiety and Depression Scores (DASS-21): For depression, the cutoff values for mild, moderate, and severe depression are 10, 14, and 21, respectively; for the anxiety scale, the cutoff values for mild, moderate, and severe anxiety are 8, 10, and 15, respectively; for the stress scale, the cutoff values for mild, moderate, and severe stress are 15, 19, and 26, respectively.

(2) Surface Electromyography of the Pelvic Floor Muscles: Participants will lie in a supine position, with their upper and lower bodies forming an angle of approximately 120°, and their feet naturally rotated outward. An electrode will be placed in the rectum to collect surface electromyography data from the pelvic floor muscles, while abdominal electrodes will monitor abdominal muscle activity. Before the examination, participants will be instructed to urinate and defecate, taught how to properly contract and relax the pelvic floor muscles, and informed about the assessment process. They will learn how to quickly contract and hold the contraction for 10 seconds. Participants will contract and relax their pelvic floor muscles based on verbal prompts to record surface electromyography values.

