**Appendix 2**

Table 1 SPIRIT schedule

| Research Phase  Project Name | Before Treatment | First Week Treatment | Second Week Treatment | Third Week Treatment | Fourth Week Treatment | 8 Weeks After Treatment |
| --- | --- | --- | --- | --- | --- | --- |
|  | t0 | t1(5days) | t2(5days) | t3(5days) | t4(5days) | t5 |
| Screening for Enrollment | √ |  |  |  |  |  |
| Medical history and basic information | √ |  |  |  |  |  |
| Routine examinations | √ |  |  |  | √ |  |
| Informed Consent Form | √ |  |  |  |  |  |
| Drug treatment | √ | √ | √ | √ | √ | √ |
| Pelvic Pain Scale/NIH-CPSI Score | √ | √ | √ | √ | √ | √ |
| DASS-21Score | √ | √ | √ | √ | √ | √ |
| SF-36 Quality of Life Scale | √ | √ | √ | √ | √ | √ |
| Surface electromyography of the pelvic floor muscles | √ | √ | √ | √ | √ | √ |
| Pudendal nerve motor evoked potentials | √ | √ | √ | √ | √ | √ |
| Bilateral magnetic stimulation |  | √ | √ | √ | √ |  |
| Peripheral magnetic stimulation |  | √ | √ | √ | √ |  |
| Fake stimulus |  | √ | √ | √ | √ |  |
| Follow-up |  |  |  |  |  | √ |
| Adverse Event |  | √ | √ | √ | √ | √ |
| Analysis of missing items and non-respondents. |  |  |  |  |  | √ |

Note: Routine examinations include: complete blood count, liver function, kidney function, and electrocardiogram examination. Pelvic pain scale, Female Pelvic Pain Scoring Scale; NIH-CPSI, The National Institutes of Health Chronic Prostatitis Symptom Index (NIH-CPSI); SF-36,SF-36 scale of quality of life; t0, enrollment; t1, At the end of 5 sessions;t2,At the end of 10 sessions; t3,At the end of 15 sessions; t4,At the end of 20 sessions; t5, Follow-up visit 8 weeks after treatment ends.

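### As printed, NIH-CPSI item 9 asks men to forecast their life without treatment but is scored as current quality-of-life impact, so up to 6 points of the total may not track improvement

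*Protocol*

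**What the plan says.** The Plan Summary names the NIH-CPSI as the main efficacy measure for men. Section 8.1 describes it as covering pain, "urinary symptoms, and the impact on quality of life, with a total of nine questions". Appendix 2 schedules the "Pelvic Pain Scale/NIH-CPSI Score" before treatment (t0), at the end of each treatment week (t1 to t4) and 8 weeks after the course (t5).

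Appendix 4 prints the form. Its instruction line is "The following symptoms are graded based on the severity of the past week". Items 7 and 8, on the effect of symptoms on daily life and thoughts, run from 0 to 3 ("None | Little | Some | A lot"). The last item stands under its own quality-of-life heading and asks "If left untreated, how do you think your life will be in the future". Its seven answers run from 0 to 6, and the upper end reads "Just so so | Mostly unsatisfactory | Unhappy | Fearful".

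The scoring block sums 7+8+9 as the impact of symptoms on quality of life and 1 to 9 as the overall rating. It prints a separate pain and discomfort score from items 1 to 4. The protocol nowhere words item 9 differently or leaves it out of the total.

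**The concern.** The item is scored as present impact on quality of life but asks for something else: a prediction of the future under a condition, no treatment, that the trial sets out to change. A man whose symptoms have eased and who credits the stimulation can truthfully give the same answer as at t0, or a worse one. A man who has not improved but expects the illness to pass can score low.

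The meaning of the question also shifts over the schedule. At t0 it describes a patient before stimulation. At t1 to t3 it is a counterfactual for a man under treatment. At t5 stimulation ended 8 weeks earlier. Change from t0 on this item is therefore not clearly like for like.

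At stake is the responsiveness of the quality-of-life score, of the overall rating and, if the overall rating is what is analysed, of the men's primary outcome.

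**Working it through.** **Inputs (Appendix 4).** Stated maximum for items 1 to 6: 31. Stated maximum of the overall rating: 43. Item 7: 0 to 3. Item 8: 0 to 3. Item 9: 0 to 6.

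**Reproducing the form's own maximum.** 31 + 3 + 3 + 6 = 43, which agrees. Item 9 is therefore inside the 43.

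**Share of item 9 on the stated bands.**
- Overall rating: 6/43 = 14.0%. If the item does not move at all, the total can fall by at most 43 − 6 = 37 points.
- Quality-of-life score: maximum 3 + 3 + 6 = 12, so the share is 6/12 = 50%.

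**Sensitivity to how the grid is summed.** The stated 31 does not follow from the printed 0-to-5 grid, so the denominator is uncertain.
- Four pain areas scored 0 to 5 each: 20 + 5 + 5 + 10 = 40 for items 1 to 4. Adding 5 + 5 for items 5 and 6 gives 50, and adding 12 gives 62. Share: 6/62 = 9.7%.
- Item 1 scored once, 0 to 5: 5 + 5 + 5 + 10 = 25, then 35, then 47. Share: 6/47 = 12.8%.

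The 6 points and the 50% are the same in every case. Only the share of the total varies, from 9.7% to 14.0%.

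**Illustration of power.** Section 5.1 gives α = 0.05, β = 0.1, effect size 0.5 and about 54 patients. A one-way ANOVA of three groups with f = 0.5 gives N = 54 at power 0.902, so the planned figure is reproduced. Assume that the effect is spread over items in proportion to their points, that item 9 contributes none of it, and that the standard deviation is unchanged. Then f = 0.5 × (1 − 6/43) = 0.43, and power at N = 54 is 0.79. With a maximum of 62, f = 0.5 × (1 − 6/62) = 0.45 and power is 0.83. At the planned enrolment of 66 with no dropout, the two powers are 0.87 and 0.90. These figures treat every patient as scored on the NIH-CPSI total. Women use another scale and the number of men is not stated, so they are an outer case and not an estimate.

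**Which score is primary for men.**
- Pointing to the total: the Plan Summary names the NIH-CPSI without restriction, and section 8.1 describes all three parts and all nine questions.
- Pointing to items 1 to 4: section 5.1 takes pain scores as the primary measure, section 8.1 is headed as a pain score, and Appendix 4 prints a pain score that excludes item 9.

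The protocol does not settle it.

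**The case against.** **The men's primary outcome may not contain item 9.** A reader might infer from the Plan Summary that the primary is compromised. The documents do not go that far: if the planned score is items 1 to 4, item 9 affects only the overall and quality-of-life scores. This stands and limits the point.

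**The wording may come from translation.** The protocol keeps Chinese numerals in some headings and the trial runs at a Chengdu hospital, so patients presumably complete a Chinese form that is not shown. If that form is sound, correcting the English appendix changes no data. This also stands, and it makes checking the form in use the first step. Still, the printed wording is the only one the protocol gives.

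**The clash with the past-week instruction is weak.** That line governs symptoms, and item 9 sits under a separate heading. This is fair. The firmer mismatch is with the scoring label, which treats the item as symptom impact on quality of life, and with section 8.1, which describes that part in the same way.

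**Non-response is conjecture.** At t5 a man has had no trial stimulation for 8 weeks, so being untreated is close to his actual state (oral medication is still allowed), and one who has improved may well forecast a better life. This holds for t5, less so for t1 to t3. A reader might also infer that the item moves differently by arm, because the peripheral group receives no sham transcranial procedure and its men could guess their allocation. But belief about allocation can colour any patient-reported item, and nothing in the protocol shows an effect specific to this one. Both are risks and not demonstrated effects.

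**Conclusion.** The point holds in limited form. Appendix 4 as printed puts a forecast under no treatment into a score meant to register present impact and repeated to detect change. Up to 6 points may not follow improvement: 14.0% of the total on the form's stated maximum, 9.7% if the grid is summed to 62, and half of the quality-of-life score.

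This rests on the patients' form carrying the printed wording and on at least some men answering it literally. For the men's primary outcome it rests also on the total being the score analysed, which is the likelier reading but is not stated. It does not concern women. The documents do not support saying that the primary is invalid, that the item is certain not to respond, or that it biases the comparison between arms. Nor do they justify moving the men's primary to items 1 to 4, which would be a change of endpoint.

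**What to change.** 1. Check item 9 on the form that patients actually complete. If it asks about living with present symptoms, correct only the English appendix.
2. If it carries the printed wording, reword it to ask how the patient feels about living with his symptoms as they were in the past week, keep the 0-to-6 scale, and use that wording from t0 onward.
3. If patients have already answered the printed wording, keep the planned men's primary score. Add a sensitivity analysis of the total without item 9 and report item 9 separately.
4. State in section 8.1 whether the planned score is the total or items 1 to 4. This clarifies the existing plan and shows whether the primary is touched.

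The cost is one line on the form, one sentence in section 8.1 and, if needed, one extra analysis, with no added patients or visits. The drawback is that scores collected on the old wording are not fully comparable with later ones. A man whose t0 answer used the old wording has no clean change score on item 9, which is why the analysis without that item is needed.
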